#### Drop-out criteria for patients from the interventional group

When the intervention takes place, paramedics can refuse to use the app at any time. They are not to use the app when it presumably places the patient or themselves at risk (e.g. rescue operation on a busy and unblocked motorway). Furthermore, the app is not to be used in emergencies with immediate action implications (e.g. cardiopulmonary resuscitation or transport to the hospital necessary without any delay) or if the patient has a severe limitation of consciousness. If patients do not speak languages provided in the app (cp. Table 2), they are excluded from the interventional group but serve as control patients in group 2. Patients who meet the eligibility criteria but with whom paramedics do not use the intervention will be analysed separately.

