### Clinical trial

In order to evaluate the effect of the developed app, we will conduct a prospective open intervention study. The main purpose of the clinical trial is to assess how the use of the app affects the perceived quality of understanding of non-German-speaking patients from the paramedics’ point of view **(primary outcome)** and how it affects the quality and quantity of information obtained from patients with language barriers **(secondary outcome).** In addition, we will assess whether the tool is perceived as helpful and easy to handle in daily use by the paramedics.

For this purpose, two different patient control groups are recruited and compared with one interventional patient group. Control group 1 consists of German-speaking patients, whereas control group 2 consists of non-German-speaking patients with whom the communication tool is not used. The interventional group consists of non-German-speaking patients with whom paramedics use the tool to communicate with patients. German-speaking control group 1 serves as baseline for on-scene times, intubation rates, and requests for on-scene emergency doctor support. The recruitment period for this group will be at least 12 months because a very large total number of cases is necessary for the selection of matched control groups. By comparing data on control group 2 and on the interventional group, the immediate effect of the tool on communication and information gathering with non-German-speaking patients can be analysed.

As to the primary outcome, we expect that using the tool, paramedics perceive the communication with non-German-speaking patients as easier and more fruitful. Therefore, we will analyse paramedics’ feedback on questionnaires for each emergency drive with foreign-language patients concerning the communication and mutual understanding with patients (see below). Paramedics are asked to report their experience with the tool to assess its acceptance and usability (see above).

Moreover, this study attempts to generate first knowledge about the extent and relevance of language barriers in emergency operations. With regard to the secondary outcome (quality and quantity of information obtained from the patient), we will be able to compare non-German-speaking patients with German-speaking patients and take demographic and medical aspects into account.

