#### Inclusion criteria for patients

Patients who meet the following criteria are eligible to participate in the study:
Control group 1: German-speaking patients of all ages who do not use the app.Control group 2: Non-German-speaking patients of all ages who do not use the app (i.e. within the first period of recruitment and because of drop-out in the second recruitment stage)Interventional group: Non-German-speaking patients of all ages who speak one of the available languages (cp. Table 2) and who are responsive to use the app.

**Table 2 Tab2:** Supported languages

• Arabic: possible dialects are Syrian Arabic, Egyptian Arabic, Moroccan Arabic (spelling Modern Standard Arabic) • Bosnian • Croatian • Czech • Dari • English • French	• Italian • Kurdish: possible dialects are Sorani and Kurmanji • Lithuanian • Pashto • Persian • Polish • Russian • Serbian • Turkish

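### The intervention group and control group 2 are selected by different rules, yet their difference is read as the effect of the app

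*Protocol article*

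**What the plan says.** The primary outcome concerns "how the use of the app affects the perceived quality of understanding of non-German-speaking patients from the paramedics" point of view (Protocol article, Clinical trial). The same section names the contrast that is to answer it: "By comparing data on control group 2 and on the interventional group, the immediate effect of the tool on communication and information gathering" is to be assessed.

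Under Inclusion criteria for patients, the intervention group is limited to non-German-speaking patients "who speak one of the available languages (cp. Table 2) and who are responsive to use the app". Control group 2 is non-German-speaking patients of any age "who do not use the app (i.e. within the first period of recruitment and because of drop-out in the second recruitment stage". It has no language, responsiveness or urgency condition.

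The section on drop-out criteria narrows the intervention group further: "the app is not to be used in emergencies with immediate action implications", nor "if the patient has a severe limitation of consciousness", nor where its use would put patient or staff at risk. Of patients whose language is not supported it says that "they are excluded from the interventional group but serve as control patients in group 2". Its last sentence sends patients who meet the eligibility criteria, but with whom the app was not used, to a separate analysis.

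Data analysis of the clinical trial names chi-squared and Mann-Whitney tests and correlation analyses. Matching by age, sex, condition and emergency situation is planned only for comparing German-speaking with non-German-speaking patients.

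**The concern.** A comparison of app users with non-users measures the app only if the non-users could have been users. Here part of control group 2 could not have been. First-phase recruitment takes in patients with unsupported languages, impaired consciousness or time-critical conditions, and in the second phase unsupported-language patients are added by rule. Such patients are plausibly harder to understand whatever tool is at hand, and less information is likely to be obtained from them. Both the perceived quality of understanding (primary) and the information obtained (secondary) could then differ between the groups even if the app did nothing. More recruitment would not help, because the difference comes from the group definitions and not from sampling error.

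**Working it through.** **Step 1: the definitions side by side.**

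| Condition | Intervention group | Control group 2, first phase | Control group 2, second phase |
|---|---|---|---|
| Supported language | required | not required | unsupported languages added by rule |
| Responsive | required | not required | not required; depends on how drop-outs are routed |
| No immediate-action emergency | required | not required | depends on how drop-outs are routed |
| No severe limitation of consciousness | required | not required | depends on how drop-outs are routed |

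The routing is unclear because two sections differ. The inclusion criteria place second-phase drop-outs in control group 2. The last sentence of the drop-out section takes eligible non-users out for separate analysis. A responsive speaker of a supported language in a time-critical emergency fits either description, as does an eligible patient with whom the paramedic declined to use the app. On either reading the first-phase column and the unsupported-language rule stand.

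**Step 2: inputs for an illustration.** The article states no figure for this bias, so there is none to reproduce. It gives 50 to 75 patients per group and 200 to 300 in total (Sample size estimation); 300 split over two groups is 150 each. It does not give the ineligible share *f* of control group 2, the shift *d* in their rating, the standard deviation, the rating scale (the questionnaire is in an additional file) or alpha. Assumed: *f* = 10–50%, *d* = 0.5–1 SD, two-sided alpha 0.05, no app effect.

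**Step 3: formula.** The spurious mean difference is *f* × *d*. It does not depend on sample size. With unit variance within each type of patient, the averaged SD is √[(2 + *f*(1−*f*)*d*²)/2], and the rejection probability is Φ(δ − 1.96) + Φ(−δ − 1.96), where δ = *f d* / (SD × √(2/n)).

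Example with *f* = 0.3, *d* = 1, n = 75:
- difference = 0.3 × 1 = 0.30 SD
- SD = √[(2 + 0.21)/2] = 1.051
- standard error = 1.051 × √(2/75) = 0.172
- δ = 0.30/0.172 = 1.75
- rejection probability = Φ(−0.21) + Φ(−3.71) ≈ 0.416

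**Step 4: Mann-Whitney simulation** on an assumed 5-point rating (4,000 runs per setting, no app effect):

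| Share *f*, shift *d* | Spurious difference | n = 50 | n = 75 | n = 150 |
|---|---|---|---|---|
| 0 (same criteria in both groups) | 0 | 4.8% | 5.1% | 5.7% |
| 10%, 1 SD | 0.10 SD | 7.2% | 8.3% | 11.3% |
| 30%, 0.5 SD | 0.15 SD | 9.7% | 14.9% | 21.7% |
| 30%, 1 SD | 0.30 SD | 25.3% | 36.5% | 60.7% |
| 50%, 1 SD | 0.50 SD | 59.2% | 76.2% | 96.8% |

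The mildest corner of the assumed range (10%, 0.5 SD) was not among these settings. The formula gives 6.1% for it at n = 75. At 75 per group the assumed range therefore runs from about 6%, barely above nominal, to 76%, and the simulated settings from 8% to 76%. The first row shows that equal criteria remove this source of error.

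**The case against.** Several objections have force.

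- **The groups overlap.** One might infer that control group 2 consists of exactly the patients whom the intervention group excludes. It does not: first-phase controls also include patients who would have qualified for the app. That dilutes the bias without removing it.
- **The explicit routing covers language only.** The sentence sending patients to control group 2 names unsupported languages, not unresponsive or time-critical patients. Those enter through unrestricted first-phase recruitment and, on one reading, as second-phase drop-outs.
- **Hard-to-reach patients are not confined to the control group.** The article plans app use through relatives or other third parties when a patient cannot speak (Development and content of the application software).
- **The net direction is not settled.** App use is left to the paramedic. If it is skipped where communication already works, easy cases leave the intervention group while their counterparts stay among first-phase controls. That works against the app.
- **The unsupported share is unknown.** Six of the 15 listed countries of origin (Rumania, China, Kosovo, Bulgaria, Greece, Spain) have a main language outside Table 2, which might suggest a large share. But these are countries, not patients. The first four in the list (Turkey, Syria, Poland, Italy) are covered, and a patient may be reached in a supported second language.
- **Severity is to be considered.** The abstract says so, and Glasgow Coma Scale, NACA score and conditions are collected. Adjustment detail may well stand in an analysis plan not shown. However, the article names no method for this contrast, severity does not cover language, and the point concerns group definitions that the article itself fixes.

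**Conclusion.** The point holds as a flaw in how the main contrast is defined. The two groups are admitted under different criteria, the stated analysis does not correct for this, and the difference is still attributed to the tool. This should be corrected before the comparison is made.

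The size is open. The spurious difference is the ineligible share times their rating deficit: 0.05 SD (0.1 × 0.5) to 0.50 SD (0.5 × 1) under the assumed ranges, with false rejection at 75 per group of about 6% to 76%. The share, the deficit, the 5-point scale and alpha are all assumptions. So is the premise that ineligible patients are rated worse, although it is plausible. A reader might conclude that a benefit of the app is guaranteed by the design. The article does not support that, because this component probably favours the app while discretionary use could pull the other way. What does follow is that a difference between these groups, in either direction, could not be attributed to the app alone.

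**What to change.** 1. For the primary and secondary comparisons, restrict control group 2 in both phases to patients who meet the intervention group's own stated criteria: a Table 2 language, responsiveness, and none of the stated reasons for not using the app. Use recorded language, initial Glasgow Coma Scale, NACA score and conditions as proxies.
2. Report unsupported-language and other ineligible patients separately and descriptively, not as controls for the app effect.
3. Confirm that the questionnaire records the patient's language, including any supported second language, from the first phase on. The list of items taken from the rescue protocols (Table 1) has no language field, and app logs exist only where the app was used.
4. Reconcile the inclusion criteria, which put second-phase drop-outs into control group 2, with the last sentence of the drop-out section, which analyses eligible non-users separately.

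The cost is revised wording in the inclusion, drop-out and data analysis sections, a smaller control group 2, and possibly one added questionnaire item. The proxies are imperfect: nothing in Table 1 directly records whether immediate action was needed. Restriction also leaves selection through paramedics' discretion in place, so that should be stated as a remaining limitation.

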**Methods:**

To consider the complex situations of paramedic care and to meet paramedics’ demands, we use an action-oriented research approach to develop the tool. We include the staff of the participating emergency medical service stations and software designers in our approach. The tool is then used and evaluated within an open interventional, non-randomised study with two control groups. Control group 1 (German-speaking patients) and control group 2 (non-German-speaking patients treated without the tool) are recruited starting from the first study phase. In the second study phase, an intervention group is additionally recruited, i.e. non-German-speaking patients with whom the tool is used.

The primary outcome of the clinical trial is improved communication with non-German-speaking patients in emergencies by means of the communication tool. The secondary outcome is an improved quality and quantity of the collected information. We exploratively observe on-scene times, demands for emergency physicians, and the usage of the intervention. By recording patients’ clinical parameters, we consider the severity of the health restrictions.

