#### Recruitment and informed consent

Within the clinical trial, data are collected about two different parties. On the one hand, patients from whom medical and demographic data are collected, and on the other hand, paramedics, who express their perspective on the communication with patients, their asssessment of the app, and of whom data will be collected when they use the app. All these data will be collected anonymously. Whether paramedics use the app is exclusively their decision and responsibility. Clear rules will be put in place so that under no circumstances rescue personnel or patients are endangered because of use of the app. Using the app and participating in the study is voluntary. Paramedics need to declare written informed consent (see above).

No written consent is obtained from the patients because it can be assumed that their well-being is not endangered by the intervention. Obtaining informed consent is desirable, but under the circumstances of an emergency operation, we would meet insurmountable hurdles with obvious ethical conflicts. Adequate informed consent seems hardly possible with patients in extreme medical situations and who do not speak German. In addition, giving adequate information would prolong the time span of the rescue mission and delay transport and thereby endanger patients and paramedics alike. Obtaining an informed consent retrospectively is likewise associated with obstacles because study participants may come from abroad, and collecting contact details (telephone number, name, address) – and explaining why these are asked for – is equally difficult in an emergency situation (and some patients may not wish to give their contact details, e.g. due to their residence status). However, if a patient objects to communicating via the device, paramedics will abort the use. Only anonymised patient data are collected, and this is done in a way that effectively prevents retrospective identification.

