#### Data analysis of the clinical trial

Characteristics of intervention and the two control groups are analysed using descriptive statistics regarding their demografics, medical conditions, assessed communication and native languages (where applicable), and aspects of the emergency operation. Differences between patients of the intervention group and the control groups will be tested for statistical significance using Chi-squared or Mann-Whitney *U*-Tests where applicable. In addition, the groups will be compared according to the recruitment centres in which patients were recruited. Relations between medical aspects of the emergency operation or demographic aspects and the assessed mutual understanding will be analysed using correlation analyses. Changes between control group 2 and the intervention group as to the perceived quality of understanding and to the quantity and quality of obtained information of patients will be analysed using paramedics’ feedback on questionnaires and comparing the content of the free text fields in the DIVI-protocols. In order to enable a comparison between non-German-speaking and German-speaking patients, a control group matched by age, sex, medical condition, and emergency situation will be drawn from the very large group of the German-speaking patients. Then, for example, on-scene times, rates of intubations, and requests for on-scene emergency doctor support can be compared.

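### App users from phase 2 are compared with a control group that mixes phase-1 patients of any language with phase-2 patients whose language the app lacks, so rating drift and language mix can pass as an app effect

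*Protocol article*

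**What the plan says.** The abstract (Methods) places the app group in the second phase only: "In the second study phase, an intervention group is additionally recruited". Both control groups are recruited from the first phase on.

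The section Inclusion criteria for patients defines control group 2 as non-German speakers without the app, "within the first period of recruitment and because of drop-out in the second recruitment stage". The section on drop-out criteria states that phase-2 patients who speak none of the supported languages are not in the intervention group: "they are excluded from the interventional group but serve as control patients in group 2". The same section treats another kind of non-use differently: "Patients who meet the eligibility criteria but with whom paramedics do not use the intervention will be analysed separately". Under Recruitment and informed consent, use is left to the crew: "Whether paramedics use the app is exclusively their decision and responsibility".

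The primary outcome is the paramedics' own rating of understanding, in an open study. The section Data analysis of the clinical trial gives the contrast: "Changes between control group 2 and the intervention group as to the perceived quality of understanding". It names chi-squared or Mann-Whitney tests and a comparison by recruitment centre. Matching is described only for the comparison with German speakers. The section Clinical trial says that from the comparison of control group 2 with the intervention group "the immediate effect of the tool on communication and information gathering with non-German-speaking patients can be analysed".

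**The concern.** The outcome is subjective, and the people who give the rating also use the tool. During the control phase, staff at the same stations take part in focus groups, case conferences, role play and reviews of cases with non-German-speaking patients (section on the action-oriented research approach). Their skill, expectations and attention to language barriers may change before phase 2 for reasons other than using the app. German-speaking patients cannot show such a change, because the questionnaire is completed only for patients whose native language is presumably not German.

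Patients without a supported language are rated by crews of the same stations in both phases and do not get the app in either. Their change from phase 1 to phase 2 is the nearest thing in this design to an estimate of drift. Once the phase-2 part is merged with phase-1 controls, that information no longer shows in the result. The merger also enriches control group 2 with languages that the app group does not contain. If such patients are harder to understand, this favours the app.

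**Working it through.** **The plan's own figure.** The sample size section takes 1200 persons with limited German and 108 operations per 1000 inhabitants per year: 1200 × 108/1000 = 129.6, which agrees with the stated 130 cases. The 50 to 75 per group comes from a citation, without alpha, power, effect or SD, and cannot be rebuilt. The point below does not depend on either figure. I use 75 per group as the upper end of the stated range.

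**Is the stratum likely to be empty?** No. The section Study site and study setting lists Rumania, China, Bulgaria, Greece and Spain among the main countries of origin. The main languages of these countries are not in Table 2.

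**The contrast.** Let A be the app effect, D the drift in ratings from phase 1 to phase 2, L the amount by which unsupported-language patients are rated worse, u their share of non-German-speaking patients, and w the phase-2 share of control group 2. With equal phase volumes, w = u/(1+u). None of D, L, u or the rating SD (set to 1) is in the documents.

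- Planned pooled contrast: A + (1−w)D + [(1−w)u + w]L = A + D/(1+u) + [2u/(1+u)]L.
- App users against phase-1 speakers of Table 2 languages: A + D.
- Difference-in-differences, (supported phase 2 − supported phase 1) − (unsupported phase 2 − unsupported phase 1): A, if drift is the same in both language strata.

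| u | w | Weight on D | Weight on L | Language-mix bias if L = 0.3 SD | False-positive rate, D = 0.2, L = 0, A = 0, 75 per group |
|---|---|---|---|---|---|
| 0.1 | 0.09 | 0.91 | 0.18 | 0.05 SD | 20% |
| 0.2 | 0.17 | 0.83 | 0.33 | 0.10 SD | 18% |
| 0.3 | 0.23 | 0.77 | 0.46 | 0.14 SD | 16% |
| 0.4 | 0.29 | 0.71 | 0.57 | 0.17 SD | 14% |

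The last column is a two-sided 5% normal approximation with SE √(2/75) = 0.163. Simulating a Mann-Whitney test on an assumed 5-category rating gives about 12% to 19% over the same range of w. If every control came from phase 1, the figure would be 20% to 21% by simulation and 23% by the normal approximation. These are upper bounds for the planned group.

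**Precision of the checks**, at an assumed 75 supported and 30 unsupported patients per phase:

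- Control group 2 is 75 + 30 + 30 = 135, so w = 30/135 = 0.22 and the weight on drift is 0.78.
- Negative control (unsupported, phase 2 − phase 1): SE √(2/30) = 0.26 SD, 95% interval about ±0.51 SD. Power to detect a drift of 0.2 SD is about 12%.
- Difference-in-differences: SE √(2/75 + 2/30) = 0.31 SD, against 0.16 SD for supported phase 2 − supported phase 1. Power for a true app effect of 0.5 SD is about 37%.

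**The case against.** **A reader might infer that pooling causes the drift bias.** It does not. The bias comes from the non-concurrent phase-1 controls, and adding phase-2 patients lowers the weight on drift from 1 to about 0.7 to 0.9. Simply dropping these patients would raise it. The fault in pooling is that it hides the check and adds unequal language mix.

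**A reader might infer that these are the only concurrent app-free patients, and that they go without the app purely by language.** That is too strong. Patient objection, severe limitation of consciousness and the need for immediate action also lead to non-use. The aim of the study allows any language in which the patient is proficient, and Table 2 includes English, French and Russian, so a Romanian or Greek patient with usable English is eligible. Whether a patient shares a supported language is partly a judgement made on scene. What stands is that this series depends less on crew choice and severity than the others.

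**An analysis plan not shown could split the group by phase.** It could, and the protocol does not delete dates or languages. But the protocol fixes the assignment to one group, names two-group tests on it and announces what the result will mean. Nor would a period term alone suffice. App users are all in phase 2, and eligible non-users are set aside. Drift could then be estimated only from the unsupported-language patients, which is the difference-in-differences above.

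**The check is weak and rests on parallel drift.** Both are true. Crews used to the app might rate missions where it is no help more harshly, which would inflate the corrected effect. For these reasons it must not decide whether an effect may be claimed.

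**Conclusion.** The point holds as stated in the heading. The assignment rule and the primary contrast are fixed in the protocol, and together they let between-phase drift and unequal language mix count as an effect of the tool. Under equal phase volumes and 10% to 40% unsupported-language patients, 71% to 91% of any drift is credited to the app. If those patients are rated 0.3 SD worse, language mix adds 0.05 to 0.17 SD in the app's favour. With an assumed drift of 0.2 SD and no app effect or language difference, the false-positive rate at 75 per group is about 12% to 20%.

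The size of drift, the unsupported share, the SD and the 5-point scale are assumptions. The documents do not show that drift will occur, nor that the final result will be false. They show that the planned comparison could not reveal it. This should be changed, but it does not invalidate the study.

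**What to change.** 1. Amend Inclusion criteria for patients and the drop-out section so that unsupported-language patients form an identified stratum, by phase, and are not merged into one control group 2.
2. For the primary outcome, compare app users with phase-1 patients who speak a Table 2 language. This removes the language-mix term but leaves the full drift, so it should be reported together with item 3.
3. Report the phase 2 minus phase 1 rating difference in unsupported-language patients as a negative control. Give the difference-in-differences as a prespecified sensitivity analysis, with its confidence interval and the parallel-drift assumption stated. Do not make either a condition for claiming an effect.
4. Define the stratum in the same way in both phases, from the language recorded for each mission. Use native language if second-language ability is not recorded in phase 1.
5. Temper the statement in the section Clinical trial about the immediate effect of the tool.

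**Cost.** No extra recruitment is needed. The questionnaire already covers these missions, but the team must confirm that it records language in phase 1, since its content is in an additional file that is not shown. The price is precision: at the assumed numbers the SEs are 0.26 SD for the negative control and 0.31 SD for the corrected contrast, so a modest drift could go undetected.
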